#### Primary outcome

2.4.1

The ISI was selected as the primary outcome measure based on evidence from previous meta-analyses and studies with similar designs (Behrendt et al., 2020; Schuffelen et al., 2023; Ritterband et al., 2009). This 7-item self-report questionnaire assesses insomnia severity over two weeks, covering sleep difficulties, dissatisfaction, impairment, and distress. Scores range from 0 to 28, with higher scores indicating greater severity. Score ranges correspond to the following severity levels: 0–7 (no clinically significant insomnia), 8–14 (subthreshold insomnia), 15–21 (moderate insomnia), and 22–28 (severe insomnia) (Cho et al., 2014; Bastien et al., 2001; Morin et al., 2011).

#### Secondary outcomes

2.4.2

The Epworth Sleepiness Scale (ESS) measures daytime sleepiness by evaluating the likelihood of falling asleep in eight daily situations (Johns, 1991; Cho et al., 2011). Each item is rated on a 4-point scale, yielding a total score ranging from 0 to 24. Higher scores indicate greater daytime sleep propensity. Scores are interpreted as follows: 0–10 (normal), 11–12 (mild), 13–15 (moderate), and 16–24 (severe) daytime sleepiness. Although individuals with chronic insomnia typically report fatigue and cognitive tiredness rather than excessive physiological sleepiness, the ESS was included to explore potential improvements in perceived daytime functioning following treatment.

The Dysfunctional Beliefs and Attitudes about Sleep (DBAS-16) assesses maladaptive sleep-related cognitions (Morin et al., 2007; Yu et al., 2009). It consists of 16 items, each rated on a 10-point scale, with higher scores reflecting stronger dysfunctional beliefs about sleep.

The Patient Health Questionnaire-9 (PHQ-9) evaluates depressive symptoms over the past two weeks (Martin et al., 2006; Park et al., 2010). It consists of nine items, each scored on a 4-point scale, with higher scores indicating greater severity. Total scores range from 0 to 27, categorized as follows: 0–4 (none/minimal), 5–9 (mild), 10–14 (moderate), 15–19 (moderately severe), and 20–27 (severe depression).

The Generalized Anxiety Disorder-7 (GAD-7) assesses generalized anxiety symptoms over the past two weeks. It includes seven items, rated on a 4-point scale, with higher scores indicating greater severity. Total scores range from 0 to 21 and are interpreted as: 0–4 (minimal), 5–9 (mild), 10–14 (moderate), and 15–21 (severe anxiety) (Spitzer et al., 2006; Lee et al., 2022).

The Short Form-36 (SF-36) measures health-related quality of life across eight domains, including physical functioning, mental health, social functioning, and general well-being (*J Health Info Stat.*, 2003; Ware Jr. and Sherbourne, 1992). Scores range from 0 to 100, with higher scores indicating better health status.

The Work Productivity and Activity Impairment Questionnaire–Specific Health Problem (WPAI-SHP) evaluates the impact of insomnia on work productivity and daily activities. It consists of four subscales: absenteeism, presenteeism, overall work impairment, and daily activity impairment (Reilly et al., 1993). Higher scores reflect greater impairment in work and daily functioning.

#### Exploratory outcomes

2.4.3

Exploratory outcomes will be assessed only in the IG.

The SleepQ mobile application includes a daily sleep diary feature, allowing participants to log sleep efficiency (SE), total sleep time (TST), sleep onset latency (SOL), and wake after sleep onset (WASO).

The system usability scale (SUS) is a 10-item standardized questionnaire that assesses the usability and user experience of the SleepQ platform (Brooke, 1996). Scores range from 0 to 100, with higher scores indicating greater perceived usability. Participants' satisfaction with the app will also be assessed using a self-designed questionnaire that evaluates acceptability, feasibility, and overall satisfaction with the intervention.

Adherence to the intervention will be measured using log files from the SleepQ platform, which capture the number of logins, dates of access, and completed modules. These data will help determine engagement patterns and intervention compliance.

#### Other outcomes

2.4.4

Data on gender, date of birth, education level, occupation, religion, marital status, residential setting, income level, smoking status, and alcohol consumption will be collected through participant self-report during the baseline assessment. Medical history, including pre-existing conditions and surgeries within the past year, current medication use, and prior treatments for insomnia or related conditions, will also be recorded.

All adverse events reported during the study will be documented in the electronic case report form. Details recorded will include the type of event, onset and end date, severity, any interventions required, outcomes, and the assessed causal relationship to the medical device.

Throughout the study, information on concomitant medications and non-pharmacological therapies will be collected. The data will include the medication's name, indication, dosage, frequency, start and end dates, and any modifications.

### Data management, monitoring, and risk management

2.5

All research staff will receive training on the study protocol to ensure standardized trial execution.

Participant data will be pseudonymized using unique identification codes and stored in encrypted, password-protected systems. A secure and access-restricted linkage file (participant key) will be maintained separately from study data and stored on a password-protected server at the coordinating institution. Only authorized members of the study team will have access to this key for the purpose of responding to participant requests or managing withdrawals.

Study data will be stored in encrypted, password-protected systems and regularly reviewed for accuracy. Investigators will monitor study progress and data completeness, with annual audits conducted by the trial data manager. Given the low-risk nature of the intervention, no formal data monitoring committee will be established.

Participants may request access to, correction of, or deletion of their personal data at any point during the study period and up to four weeks following their final participation, in accordance with the Korean Personal Information Protection Act. For statistical analysis and dissemination, the dataset will be fully anonymized and no longer traceable to individual participants.

As a non-invasive digital intervention, SleepQ is considered low-risk; however, some participants may experience temporary psychological discomfort. Psychological assessments at study time points will monitor distress, with referrals to clinical care provided if needed. Participants who withdraw from the study will be asked to provide reasons, and follow-up data collection will continue where possible. Trial insurance covers potential adverse effects, though no significant risks are anticipated. Protocol amendments will require IRB approval and will be reported in the published article.

### Planned statistical analysis

2.6

The analysis will include participants following the full analysis set based on the Intention-to-Treat principle, which includes all randomized participants who have completed a baseline assessment of the primary outcome (ISI score). All statistical analyses will be performed using SAS Software Version 9.4 or higher, with a two-sided significance level of 0.05.

Descriptive statistics will summarize baseline demographic and clinical characteristics, adherence, and usability measures. Depending on their distribution, continuous variables will be reported as means and standard deviations or medians and interquartile ranges, while categorical variables will be presented as frequencies and percentages.

To evaluate the primary outcome at post-treatment (t3, 6 weeks), an Analysis of Covariance (ANCOVA) will be conducted, adjusting for baseline values and stratification factors (study site and sleep medication use) as covariates to compare differences between the IG and the CG. Effect sizes (Cohen's d) will be reported alongside *p*-values and confidence intervals to indicate the magnitude of between-group differences. A mixed-effects model for repeated measures (MMRM) will be applied to assess longitudinal treatment effects. This model considers three repeated assessments (t1, t2, t3) as nested within individuals, accounting for intra-individual correlations and missing data. No imputation of missing values is planned, as MMRM accommodates missing data under the assumption that data are missing at random. A stepwise modeling approach will be used, beginning with a random intercept model without predictors. Next, fixed effects for time (study entrance, 2 weeks, 4 weeks) and treatment (IG vs. CG) will be added. Finally, a treatment × time interaction term will be introduced to examine whether outcome trajectories differ between groups. Treatment effects will be reported using Cohen's d as a measure of effect size. Descriptive analyses will be conducted to explore patterns of missingness, including comparisons of baseline characteristics between study completers and non-completers, as well as the timing and extent of dropout across timepoints.

Additionally, sleep diary data will be analyzed to explore trends in sleep parameters. Weekly mean values for sleep efficiency (SE), total sleep time (TST), sleep onset latency (SOL), and wake after sleep onset (WASO) will be calculated. An additional MMRM analysis will examine trends in these sleep parameters over time. Post hoc exploratory analyses may also examine potential effect modification by baseline characteristics, such as sleep medication use, alcohol consumption, and smoking status.

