## Abstract

Cognitive behavioral therapy for insomnia (CBT-I) is the first-line treatment for chronic insomnia. However, access to in-person CBT-I remains limited due to a shortage of trained providers and structural barriers. Digital CBT-I (dCBT-I) offers a scalable solution to bridge this treatment gap, yet real-world evidence of its effectiveness remains limited. This study aims to examine the effectiveness of a mobile dCBT-I intervention, “SleepQ,” in a routine clinical setting. This study is a multicenter, two-arm, open-label, randomized controlled trial comparing a mobile dCBT-I intervention to a waitlist control group. A total of 120 adults with chronic insomnia will be recruited from six clinics in South Korea. Participants will be randomly assigned (1:1) to either the intervention group receiving 6 weeks of dCBT-I or the control group, which will gain access to the intervention after the posttreatment assessment. The primary outcome is the Insomnia Severity Index score change from baseline to 6 weeks post-randomization. Secondary outcomes include dysfunctional sleep beliefs, daytime sleepiness, depressive and anxiety symptoms, quality of life, and work productivity. Exploratory outcomes include adherence, usability, app satisfaction, and sleep parameters from the integrated sleep diary. In the intervention group, follow-up assessments will be conducted 3- and 6-months post-randomization to evaluate long-term effects. This trial will evaluate the effectiveness of mobile dCBT-I for chronic insomnia within routine clinical care. Findings will contribute to the evaluation of the clinical implementation of digital therapeutics for insomnia and inform the integration of mobile-based CBT-I into routine care.

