### Trial design

2.3

This study is a multicenter, two-arm, open-label RCT designed to evaluate the effectiveness of a dCBT-I intervention. The trial follows the Standard Protocol Items: Recommendations for Interventional Trials (SPIRIT) 2013 guideline (Chan et al., 2013). The multicenter approach, involving six outpatient psychiatric clinics across South Korea, was chosen to enhance the generalizability across diverse clinical settings. Eligible participants will be randomized into either the intervention group (IG) or the waitlist control group (CG) in a 1:1 allocation ratio. The IG will receive dCBT-I (SleepQ, WELT Corp. Ltd) over 6 weeks. The CG will receive no intervention from the study team during this period but will be given access to dCBT-I upon completion of the posttreatment assessment at 6 weeks post-randomization. The waitlist design enables short-term comparison while ensuring all participants ultimately receive access to the intervention. Additionally, participants in the intervention group will be followed up at 3- and 6 months post-randomization (Fig. 1). Due to the behavioral nature of the intervention, participant blinding is not feasible. However, allocation will be concealed during statistical analysis to minimize potential bias.

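### The no-imputation rule rests on a property of the MMRM, so the primary week-6 ANCOVA covers only participants with an observed week-6 ISI and not the stated full analysis set

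*Protocol article*

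**What the plan says.** The abstract defines the endpoint: "The primary outcome is the Insomnia Severity Index score change from baseline to 6 weeks post-randomization". Section 2.6 (Planned statistical analysis) then makes four statements that bear on missing data.

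- Analysis set: a full analysis set on the intention-to-treat principle, which "includes all randomized participants who have completed a baseline assessment of the primary outcome (ISI score"). No post-baseline value is required.
- Primary test: "To evaluate the primary outcome at post-treatment (t3, 6 weeks), an Analysis of Covariance (ANCOVA) will be conducted", adjusted for baseline, site and sleep medication use.
- Second model: "A mixed-effects model for repeated measures (MMRM) will be applied to assess longitudinal treatment effects". The visits it takes in are weeks 2, 4 and 6 (t1 to t3).
- Missing data: "No imputation of missing values is planned, as MMRM accommodates missing data under the assumption that data are missing at random".

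The only other missing-data work in the section is descriptive: completers are compared with non-completers at baseline, and the timing and extent of dropout are tabulated. Section 2.7 sizes the trial on the ANCOVA and raises 97 to 120 for 20% attrition. Table 2 shows the ISI collected in both arms at t0, t1, t2 and t3.

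**The concern.** The argument for not imputing is sound for a likelihood-based repeated-measures model, but it is applied to a section whose primary test is a different model. An ANCOVA of one time point drops anyone who lacks that time point. It gains nothing from the fact that another model, fitted separately, would be valid under missing at random (MAR). The declared population and the declared method therefore disagree.

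The trial's main estimate is at stake. In an open-label comparison of an app with a waitlist, the reasons for missing week 6 may differ by arm. Controls "will be given access to dCBT-I upon completion of the posttreatment assessment at 6 weeks post-randomization", whereas intervention participants have the app from randomization. Section 2.4 holds t1 and t2 remotely and t3 in person, so some participants may have scores at weeks 2 and 4 and none at week 6. If dropout depends on early response and does so differently by arm, the observed-case ANCOVA can be biased even though the data are MAR given t1 and t2.

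**Working it through.** **Who is in the primary analysis.** Inputs from section 2.7: 97 before attrition, 20% attrition, target 120.

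- Inflation: 97 / (1 − 0.20) = 121.25, which rounds up to 122 at 1:1. The stated 120 is within 2 of this.
- Expected with a week-6 ISI: 120 × 0.80 = 96. Members of the full analysis set left out: 120 − 96 = 24.

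The inflation replaces precision (96 against the required 97). It does nothing about selection.

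**Whether the MMRM, as written, fills the gap.** Section 2.6 counts t1, t2 and t3 as the repeated assessments. Its time effect, however, lists study entry and weeks 2 and 4, so week 6 is absent. No week-6 contrast from this model is named as primary or as a sensitivity analysis.

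**Size of possible bias.** The article gives no SD, no correlations and no attrition by arm, so these are assumptions. On planning scale, d = 2f = 2 × 0.485 = 0.97, which is 4.85 ISI points at an assumed SD of 5.

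First set: 60 per arm, 2,000 simulated trials per scenario, correlations 0.5 to 0.7, true effect −4.85. Only week 6 goes missing, and any dependence is on the week-4 ISI. Overall dropout is about 20%. The full-data ANCOVA gives −4.86 or −4.87 throughout.

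| Dropout mechanism | Missing, intervention / control | Observed-case ANCOVA | MAR estimator using t1, t2 |
|---|---|---|---|
| Completely at random | 20% / 20% | −4.86 | −4.85 |
| Worse week-4 score, alike in both arms | 21% / 21% | −4.86 | −4.84 |
| Worse week-4 score, intervention arm only | 40% / 0% | −5.89 | −4.87 |
| Poor responders leave intervention, good responders leave control | 21% / 21% | −6.00 | −4.85 |

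The bias in the third row is 5.89 − 4.87 = 1.02 points, and 1.02 / 4.85 = 21%.

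Second set: 60 per arm, 1,500 simulated trials, correlations 0.45 to 0.78, true difference 3.2 points in favour of the app.

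- Intervention 31%, driven by non-improvement, and control 9% at random (mean 20%): observed-case ANCOVA 4.21, full data 3.18, MAR estimator 3.17. Bias 4.21 − 3.18 = 1.03, and 1.03 / 3.2 = 32%.
- Weaker dependence, 27% against 9%: 3.83 against 3.18 with full data, bias 0.65 (20%). MAR estimator 3.20.
- 20% completely at random: neither estimator is biased. The empirical SE is 0.920 for the observed-case ANCOVA and 0.869 for the MAR estimator, a ratio of 0.945, so about 5% smaller.

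Milder cases under similar assumptions:

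- Dropout of 25% / 15% driven by non-improvement in both arms: bias 0.1 to 0.2 points.
- The same rates with only intervention dropout outcome-driven: about 0.35 to 0.6 points.
- One run with the same mechanism in both arms: 3.02 against a true 3.2, a small understatement.

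**The case against.** The strongest reply has four parts.

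**The bias is conditional.** The article gives one attrition figure, for both arms together. When dropout is random, or depends on response alike in both arms, the observed-case ANCOVA is unbiased or nearly so. A reader might infer that the main result will be inflated in the device's favour by about a third. The documents do not support that: it needs steep, arm-specific, outcome-driven dropout, and an assumed 3.2-point effect where the planning effect corresponds to 4.85 at the same SD. This part of the reply stands.

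**Retention is supported in both arms.** Section 2.2 pays both groups the same USD 120 on completing week 6, and section 2.5 continues data collection after withdrawal where it can. Stopping the app is therefore not the same as missing t3, and a non-user with a week-6 score stays in the analysis as randomized. This stands too and may reduce the problem, but the plan still budgets for 20% loss.

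**An MMRM over the same visits is already planned, and the choice not to impute is stated openly.** Both are true. However, the article gives the MMRM no role in the week-6 primary estimate, and its listed time levels leave week 6 out.

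**Detail may sit in an analysis plan that is not shown.** That would answer a silence. Here the article states a rule and gives it a reason that does not fit its primary test. An analysis plan that followed the text would carry the mismatch forward. The attrition inflation in section 2.7 is ordinary practice and is no evidence of a fault.

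**Conclusion.** The point holds as a mismatch between three stated elements: an intention-to-treat full analysis set, a single-time-point primary ANCOVA, and a no-imputation rule justified only by another model. Followed literally, the primary test covers about 96 of 120 participants at the planned attrition and ignores the week-2 and week-4 ISI.

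The effect on the estimate is a risk and not a certainty. It ranges from about 0 to about 1 ISI point, that is up to roughly 20% of 4.85 points or 30% of 3.2 points. The range rests on an assumed SD of 5, assumed correlations and assumed dropout mechanisms. The MAR estimator was essentially unbiased in every scenario tried, but all of those scenarios were MAR by construction, so they say nothing about dropout that depends on the unseen week-6 score.

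**What to change.** Name one primary week-6 estimator whose missing-data assumption matches its justification, before analysts see results by arm. Either of these would do:

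- **MMRM over t1, t2 and t3**, with baseline ISI, site, sleep medication use, visit, arm, arm × visit and an unstructured covariance. The week-6 arm contrast is the primary estimate. Correct the listed time levels to include week 6. This uses every participant with at least one post-baseline ISI. It does not reach those with none, so it should not be described as covering all randomized participants.
- **Multiple imputation of t3**, by arm, from t0 to t2, followed by the planned ANCOVA. This keeps the whole full analysis set in the primary test.

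In either case, keep the observed-case ANCOVA as a sensitivity analysis and reword the no-imputation sentence so that its reason refers to the model it serves. A reference-based sensitivity analysis for intervention dropouts is optional and can be left to the analysis plan.

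The cost is protocol wording, modest programming and reliance on MAR. No new data are needed, and with complete data the estimate would be essentially that of the ANCOVA.

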#### Randomization and blinding

2.3.1

Participants meeting the eligibility criteria will be randomized in a 1:1 allocation by an independent researcher not involved in the study. A stratified block randomization approach will be applied, stratifying participants based on the study site and sleep medication use. Randomization will be performed via an Interactive Web-Response System, which will generate computer-randomized sequences with concealed allocation. Diagnostic interviewers conducting clinical assessments will remain unaware of participants' group assignments. After randomization, each participant will immediately receive an access code for the intervention (IG) or the information that the intervention will start in 6 weeks (CG). Due to the study design, blinding of participants and study personnel to group allocation during the intervention period is not feasible.

Group allocation will be masked by an independent researcher, who will anonymize datasets by removing identifying allocation variables before statistical procedures. Consequently, evaluators will remain blinded to intervention and control conditions throughout the analysis.

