### Statistical power and sample size

2.7

The sample size was determined using G*Power 3.1 (Faul et al., 2007), based on an ANCOVA with a fixed-effects model, assuming a large effect size (Cohen's f = 0.485) derived from previous research, which reported heterogeneous effect sizes ranging from 0.97 to 2.08 (Cohen's d) (Behrendt et al., 2020; Schuffelen et al., 2023). Cohen's f is the conventional effect size metric for ANCOVA models, and can be derived from Cohen's d. The calculation was conducted with an alpha level of 0.05, a statistical power (1- beta) of 0.90, and 3 covariates, including baseline scores and stratification factors. The G*Power analysis indicated that a total sample size of 97 participants would be required to achieve the desired power. The required sample size was adjusted to account for a 20 % attrition rate, resulting in a final target of 120 participants.

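### The longitudinal model omits baseline ISI and both stratification factors that the ANCOVA includes, and its time levels contradict its stated outcomes and leave out week 6

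*Protocol article*

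**What the plan says.** Protocol article, section 2.6, describes two analyses of the ISI.

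- **ANCOVA at week 6 (t3), the primary comparison:** "adjusting for baseline values and stratification factors (study site and sleep medication use) as covariates".
- **A mixed model for repeated measures, for the longitudinal effect:** "A stepwise modeling approach will be used, beginning with a random intercept model without predictors". Time and treatment come next as fixed effects, and the treatment-by-time interaction last. No step names baseline ISI as a covariate, site or sleep medication use.

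Section 2.3.1 makes two of these three variables randomisation factors: "stratifying participants based on the study site and sleep medication use".

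The paragraph describes the visits in the mixed model twice. The repeated outcomes are t1, t2 and t3, which the schedule in section 2.4 (Table 2) places at weeks 2, 4 and 6. The time factor is then listed as study entry, week 2 and week 4.

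The same paragraph plans no imputation. It relies on the mixed model to deal with missing scores under a missing-at-random assumption.

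**The concern.** The term list is written out in full, so the missing covariates are part of what the article states and not a gap left to a later document. Three things follow.

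1. **Precision.** Baseline ISI is normally the strongest predictor of later ISI. Leaving it out discards information that the ANCOVA beside it uses. Leaving out factors that were balanced by stratification also tends to make model standard errors too large.
2. **Which model is meant.** With outcomes at weeks 2, 4 and 6, baseline is absent altogether. With the listed time levels, baseline is an outcome and week 6 is absent. The text cannot be fitted as printed without choosing between them.
3. **Missing data.** A week-6 ANCOVA without imputation drops anyone lacking a week-6 score. The mixed model is the only described analysis that uses their earlier visits. Missing at random holds conditionally on what the model contains, so dropout related to baseline severity, site or medication is less well covered when these are left out.

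The covariance is a separate question. A random intercept on its own implies one common correlation between all pairs of visits. If it is kept as the only structure and the truth differs, standard errors can be too small.

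**Working it through.** **Inputs from the protocol article.** Significance is judged "with a two-sided significance level of 0.05" (2.6). Allocation is 1:1 (2.3.1). The target is 120 with 20% attrition (2.7), so 120 × 0.80 = 96 completers, 48 per arm. The article states no standard deviation, correlation or precision for the longitudinal model, so there is no figure of its own to reproduce. All SDs and correlations below are assumptions. The variance ratios and type I error rates do not depend on the number per arm.

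**Step 1: the two visit lists side by side.**

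| Description in 2.6 | Baseline | Week 2 | Week 4 | Week 6 |
|---|---|---|---|---|
| Repeated outcomes | no | yes | yes | yes |
| Levels of the time factor | yes | yes | yes | no |

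They agree on weeks 2 and 4 only.

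**Step 2: precision of the week-6 contrast.** Let r be the correlation between baseline and week-6 ISI, with common SD σ. Per-person variances are:

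- baseline absent: σ²
- baseline as covariate: σ²(1 − r²)
- baseline as outcome level (change score): 2σ²(1 − r)

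The ratios to the adjusted analysis are therefore 1/(1 − r²) and 2(1 − r)/(1 − r²) = 2/(1 + r).

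| r (assumed) | Baseline absent | Baseline as outcome level |
|---|---|---|
| 0.3 | 1/0.91 = 1.10 | 2/1.3 = 1.54 |
| 0.5 | 1/0.75 = 1.33 | 2/1.5 = 1.33 |
| 0.7 | 1/0.51 = 1.96 | 2/1.7 = 1.18 |

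With baseline absent, standard errors rise by factors of 1.05, 1.15 and 1.40. In sample-size terms, 96 completers then give the precision of 96 × 0.91 = 87, 96 × 0.75 = 72 or 96 × 0.51 = 49 in an adjusted analysis. The two columns belong to mutually exclusive readings and cannot be combined. The article gives nothing from which to size the further loss from omitting site and medication.

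**Step 3: calibration if the random intercept is the only covariance structure.** With complete data, the fitted model takes the average variance and average covariance over its visits. For a contrast c and covariance matrix Σ, SE = √[(2/48) c′Σc]. The model SE uses the averaged matrix and the true SE uses Σ. Type I error is 2[1 − Φ(1.96 × model SE / true SE)].

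*Worked example, listed time levels, SD 4.5, correlation 0.7 per visit step.* The correlations are 0.7, 0.7 and 0.49, mean 0.63. For the change from entry to week 4:

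- true SE = √[2 × 20.25 × 0.51 / 24] = 0.928
- model SE = √[2 × 20.25 × 0.37 / 24] = 0.790
- ratio 0.85, type I error 0.095

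*Worked example, outcomes at weeks 2, 4 and 6, SDs 4.5, 5 and 5.5.* For the week-6 difference:

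- true SE = √(30.25/24) = 1.123
- the average variance is (20.25 + 25 + 30.25)/3 = 25.17, so model SE = √(25.17/24) = 1.024
- ratio 0.91, type I error 0.074

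Four patterns were tried: equal correlation 0.5; decay at 0.7 per step with constant SD 4.5; decay at 0.75 with SDs 4, 4.5, 5, 5.5; and decay at 0.6 with SDs 3, 4.5, 5, 5.5.

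| Contrast | Equal correlation | Other three patterns |
|---|---|---|
| Week-6 difference, weeks 2–6 as outcomes | 5.0% | 5.0% to 7.4% |
| Week 6 minus week 2, weeks 2–6 as outcomes | 5.0% | 9.0% to 9.9% |
| Week 4 minus entry, listed time levels | 5.0% | 8.3% to 9.9% |
| Week 6 minus entry, all four visits | 5.0% | 9.3% to 12.2% |

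In the week-6 row, decaying correlation with constant SD still gives exactly 5.0%; only growing variance moves it.

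**The case against.** The strongest defence is that this model does not carry the primary test. Section 2.6 gives the week-6 comparison to an ANCOVA that already adjusts for baseline and both stratification factors. That is correct, and a reader who inferred that the primary p-value is at risk would be wrong.

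A second defence is that the final covariance is not fixed. The random intercept is where the build begins, the analysis is called an MMRM, and residual structure is commonly left to the statistical analysis plan. This also stands. A reader might infer that the article commits the sponsor to standard errors that are too small, with an error rate near 9%. The documents do not support that: it needs the random intercept to be the sole structure and the true pattern to depart from compound symmetry. Nor do the missing covariates cause it, since they cost precision and tend to push standard errors up. The largest error rates also come from a four-visit model that neither visit list describes.

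A reader might further infer that the stepwise build allows a favourable step to be chosen. The sequence is fixed, has no data-driven selection rule and adds the interaction unconditionally. A main-effect step would average early visits with week 6, giving (2 + 4 + 6)/3 ÷ 6 = two thirds of the week-6 effect under linear build-up, but nothing names that step as the reported estimate.

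None of this answers the omitted covariates or the contradictory time levels, both of which are in the printed text.

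**Conclusion.** The point holds in a limited form. As written, the longitudinal model omits the baseline covariate and both stratification factors used in the ANCOVA of the same paragraph, and its time levels conflict with its outcomes and lose the primary time point.

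The cost in precision is a variance 1.10 to 1.96 times the adjusted one if baseline is absent, or 1.54 down to 1.18 times if baseline is an outcome level, for assumed r from 0.3 to 0.7, equal SDs and complete data. The calibration problem is conditional. Under the assumed departures from compound symmetry, type I error is about 5% to 7% for the week-6 difference and about 8% to 12% for change-from-baseline contrasts. It is 5% if compound symmetry holds.

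This is a supporting analysis, but it is worth correcting because it is also the plan's stated answer to missing data with 20% attrition expected.

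**What to change.** Replace the stepwise paragraph with one prespecified model: ISI at weeks 2, 4 and 6 on baseline ISI, baseline by time, treatment, time, treatment by time, site and sleep medication use, with an unstructured within-person covariance. Correct the time levels to 2, 4 and 6 weeks. State that the week-6 treatment contrast from this model is reported whatever the interaction p-value.

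The cost is rewording, a few lines of SAS and some extra parameters. The added fixed effects are baseline (1), baseline by time (2), six sites (5) and medication (1), nine in all. Three visits need six covariance parameters in place of two, which 120 participants support. One limit remains: a participant with no score after baseline still contributes nothing to this model, so the number of such participants should be reported by arm.
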